### Outcome measures

An outcome assessment timeline and summary of assessment tools used is provided in Table 1.

**Table 1 Tab1:** Timeline of outcome assessment

Pre-operative (baseline)	
Baseline demographics:	Age, sex, smoking status, height, weight, diabetic history
History of back/leg symptoms:	Duration of symptoms, neurological deficit
Physical function:	ODQ, SF-36
Pain:	Back and leg pain (NRPS)
Physical activity:	IPAQ-SF
Psychological status:	Depression (PHQ-9), anxiety (GAD-7)
Post-operative (days 1–7):	
Surgical procedure:	Decompression, discectomy, fusion; single or multi-level
Accelerometry:	Time spent walking, step count, time spent in sedentary and active postures, number of walks
Pain:	Back, leg and wound pain (NRPS)
Supervised walking:	Patient/physiotherapist reported
Post-operative complications:	Complications requiring medical intervention and/or limit walking time
Post-operative (6 months):	
Physical function:	ODQ, SF-36
Patient satisfaction:	5 point likert scale
Post-operative complications:	Complications requiring medical intervention

#### Dependent variable

The primary dependent variable will be self-reported function. This will be measured using a Modified Oswestry Disability Questionnaire (ODQ) [30] and the physical component summary (PCS) of the SF-36 (version 2) [31, 32]. Back and leg pain intensity using the numeric pain rating scale (0–10) (NPRS) [33] will be recorded as secondary dependent variables. The ODQ, SF-36 and the NPRS are all validated and recommended for use within the back pain population [34], and are widely used in spinal surgery research. The modified ODQ substitutes kilometres for miles to estimate walking distance, and has been validated in the Australian population [30]. The relationship between post-operative walking and each of the four dependent variables will be analysed individually.

#### Independent (predictor) variable

The predictor variable to be used in data analysis will be the total time spent walking (recorded as total time performing stepping activity) over the first seven post-operative days. This data will be recorded using an activPAL3 accelerometer and downloaded using software provided by PALtechnologies. The activPAL3 accelerometers provide a user-friendly measure of posture and walking with robust evidence for validity and sufficient reproducibility for this study [24–26]. As the activPAL3 accelerometer is worn on the thigh, the accuracy of the monitor is not reliant on arm swing and is not expected to vary if participants are using a gait aid.

#### Independent (confounding) variables

Data will be collected for variables where there is either evidence to suggest they influence outcome following lumbar spinal surgery, or there is or strong theoretical rational for their inclusion. This will include age, gender, current smoking status [14, 15], obesity [14, 18], diabetes [14, 16, 17], depression [19, 20], duration of pain/symptoms [35], neurological deficit [14], anxiety, pre-operative activity, pre-operative mobility, surgical procedure, multi-level surgery, and pre-operative function.

Depression will be assessed using the Patient Health Questionnaire Depression Scale (PHQ-9), using a cut off score of ≥10 [36]. The PHQ-9 is a short, valid and reliable measure of depression, and has been recommended for use within the chronic back pain population [37]. Anxiety will be scored using the Generalised Anxiety Disorder 7-item Scale (GAD-7), using a cut off score of ≥10 [38]. The GAD-7 is a brief, seven question scale used to screen for, and assess the severity of anxiety. It has been validated in the general population [38]. Neurological deficit will be assessed by asking the participant if he/she is aware of any changes to the sensation or strength in their affected lower limb. This level of information is deemed appropriate for this study, as any sensory or motor deficit that the participant is unaware of is unlikely to have an impact on functional ability. Pre-operative activity will be assessed using the International Physical Activity Questionnaire Short Form (IPAQ-SF) [39, 40]. The IPAQ-SF is a brief, reliable seven item questionnaire that requires participants to report on physical activity undertaken over the previous seven day period [39, 40]. Physical activity is categorised into low, moderate and high activity levels. As it is expected that the majority of participants will report either low or moderate activity levels, the two categories of low and moderate/high activity levels will be used for data analysis. Baseline ODQ score will be used as a measure of pre-operative function. Pre-operative mobility will be categorised based on the response to Section 4 (Walking) on the ODQ. Participants will be categorised as having limited mobility if they score 3 or more - unable to walk more than 500 m, require a walking aid, or are confined to bed.

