### Study procedure

#### Recruitment and sample size

The recommended sample size for logistic regression analysis is a minimum of 5 outcome events per predictor variable (EPV) [29]. The maximum number of variables to be analysed in this study is 15 giving a minimum sample size of 150. Based on expected admissions to the treating institution over the recruitment period, it is expected that this will provide an estimated recruitment pool of 300 eligible participants and sample size of approximately 250 participants. This proposed sample size allows for variation in EVP, missing data and participants lost to follow-up.

Patients undergoing lumbar spinal surgery will be identified from the surgical lists. All eligible patients will be provided with an information pack containing a participant information statement, consent form, withdrawal of consent form and baseline outcome measures. The research physiotherapist will contact potential participants during the week prior to surgery to confirm eligibility and respond to any questions. Written consent will be obtained from all participants. Consent forms and baseline outcome measures will be collected from participants following admission to hospital. Demographic data and information about the surgical procedure will be collected from the participant and patient records during admission.

Following surgery, all participants will be fitted with an activPAL3 accelerometer (PAL technologies) to be worn for the first seven post-operative days, commencing the morning after the day of surgery. As per the manufacturer instructions, the accelerometer will be fixed to the upper thigh using a waterproof transparent Tegaderm dressing. This can then remain in place for the seven-day monitoring period, with a daily review to check for discomfort or irritation. This method of fixing the accelerometer to the thigh eliminates the need for participants to remove and apply the monitoring device for showering and sleeping, it does not require participants to wear a waist band or belt that would sit across the site of the lumbar surgery.

Where participants are discharged during the seven-day monitoring period they will be provided with information regarding the use and removal of the accelerometer, and a reply paid envelope to return the accelerometer to the researcher.

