#### Relationship between time spent walking and outcome

Multivariable logistic regression analysis will be used to investigate the relationship between the time spent walking in the first week after surgery and outcome at six months using SPSS software. The dependent variable in the logistic regression model will be the change in score on the ODQ, SF-36 (PCS), NRPS (back) and NRPS (leg) between baseline and six months. The change in scores on the ODQ, SF-36 (PCS) and NRPS will be dichotomised based on the threshold required to demonstrate a substantial clinical benefit.

Thresholds required to meet the minimum clinically important difference (MCID) have been identified for the ODQ, the SF-36 (PCS) and the NPRS [41] (Table 2). In addition, thresholds required to obtain a substantial clinical benefit (SCB), where patients report a major improvement in symptoms, have been defined for the ODQ, SF-36 (PCS) and NRPS in the lumbar fusion population [42] (Table 2). For the purpose of this study it has been assumed that SCB following lumbar fusion surgery provides a fair estimate of substantial clinical benefit following lumbar surgery in general. These thresholds allow the change in scores to be categorised as minimal improvement (below MCID threshold), moderate improvement (above MCID threshold, below SCB threshold) and substantial improvement (SCB threshold or greater).

**Table 2 Tab2:** MCID and SCB thresholds

Outcome measurement tool	MCID (points change)	SCB (points change)
ODQ	10	18.8
SF-36 (PCS)	4.9	6.2
NPRS (back)	2	2.5
NRPS (leg)	2	2.5

As all participants in this study are undergoing surgery with the aim of improving pain and physical function, it expected that the majority of participants in this study will report an improvement in scores above the MCID threshold. Therefore the SCB threshold will be used to analyse the impact of walking time on outcome (minimal/moderate improvement compared to substantial improvement). For each of the four dependent variables a multivariable logistic regression model will be generated comparing participant outcome relative to the SCB threshold.

With the exception of pre-operative function and surgical procedure, all confounding variables will be dichotomised (Table 3).

**Table 3 Tab3:** List of independent variables and classification for statistical analysis

	Classification				
1. Post-operative activity	Time spent walking (minutes)				
2. Age	1. < 65 years	2. ≥ 65 years			
3. Gender	1. Male	2. Female			

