4. Current smoking status	1. Non-smoker	2. Smoker			
5. Obesity	1. BMI < 30	2. BMI ≥ 30			
6. Diabetes	1. Not diabetic	2. Diabetic			
7. Depression	1. PHQ-9 < 10	2. PHQ-9 ≥ 10			
8. Anxiety	1. GAD-7 < 10	2. GAD-7 ≥ 10			
9. Duration of pain/symptoms	1. < median (months)	2. ≥ median (months)			
10. Neurological deficit	1. No deficit	2. Neurological deficit			
11. Pre-operative activity	1. IPAQ-SF - Mod/high	2. IPAQ-SF - low			
12. Pre-operative mobility	1. ODQ (section 4) < 3	2. ODQ (section 4) ≥ 3			
13. Surgical procedure	1. Decompression	2. Disc surgery	3. Fusion		
14. Multi-level surgery	1. Single level surgery	2. Multi-level surgery			
15. Preoperative function (ODQ%)	1. 0–20	2. 21–40	3. 41–60	4. 61–80	5. 81–100

Bivariate analyses will be carried out to assess the association between each confounding variable and each outcome measure. The variables that have an independent association with outcome will be included in the final regression model. Analysis of correlation between the independent variables will be carried out to assess for multicollinearity. Where variables are highly correlated, either the more relevant variable or the variable with the more complete data set will be retained in the final regression model [43].

Missing independent variable data will be managed based on the quantity of missing data per participant and per variable. In the case of missing or incomplete accelerometry data, participants will be removed from analysis where three or more days of recordings are missing. In the case of one to two days of missing data, the time spent walking each day will be estimated based on the mean daily walking time of the total sample population. Comparisons will be made between the characteristics of participants with and without missing data to ensure minimisation of bias [43]. The underlying assumptions of the model will be assessed using the SPSS software “goodness of fit” testing.

Bivariate analysis will be used to examine the association between post-operative walking time, and both patient satisfaction and post-operative complications as reported at six months.

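### The PCS, back-pain and leg-pain change models never adjust for the baseline of their own outcome, although it is collected; the resulting bias in the walking odds ratio has unknown size and direction

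*Protocol article*

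**What the plan says.** All references are to the protocol article.

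- **Outcomes.** Under *Relationship between time spent walking and outcome*, the dependent variables are changes between baseline and six months, and these "will be dichotomised based on the threshold required to demonstrate a substantial clinical benefit". Table 2 sets the thresholds at 18.8 (ODQ), 6.2 (PCS) and 2.5 (back and leg NRPS).
- **Models.** "For each of the four dependent variables a multivariable logistic regression model will be generated comparing participant outcome relative to the SCB threshold". Under *Dependent variable*, ODQ and PCS both measure the primary outcome, function; the two pain scores are secondary.
- **Covariates.** *Recruitment and sample size* fixes the list: "The maximum number of variables to be analysed in this study is 15 giving a minimum sample size of 150". Table 3 names the 15, namely walking time and 14 confounders. Item 15 is baseline ODQ in five bands, and item 12 is the walking section of the ODQ. *Independent (confounding) variables* explains item 15: "Baseline ODQ score will be used as a measure of pre-operative function". Neither that section nor Table 3 lists baseline PCS, back NRPS or leg NRPS.
- **Entry rule.** After bivariate analyses, "The variables that have an independent association with outcome will be included in the final regression model". Baseline ODQ is thus a candidate, not a fixed covariate.
- **Data.** The pre-operative part of Table 1 includes the SF-36 and back and leg pain scores, so every missing baseline is already collected.

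**The concern.** A change score is partly made of its own baseline. Patients who start worse have more room to improve and regress further towards the mean, so own baseline strongly predicts crossing the SCB threshold. For NRPS the link is partly arithmetic: a patient who starts at 0, 1 or 2 cannot fall by 2.5 points, however much they walk. Such patients can be enrolled, because *Participants* places no restriction on the nature of pre-operative symptoms.

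Pre-operative status may also relate to the exposure. Research question 3 asks whether restricted pre-operative function influences walking in the first week. A variable that drives the outcome and plausibly relates to the exposure meets the plan's own criterion for a confounder.

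The ODQ model at least has its own baseline as a candidate. The other three have only baseline ODQ, a different and banded scale that screening may remove. What is at stake is whether a walking association in those three models, or its absence, can be separated from baseline severity.

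**Working it through.** **1. The plan's own figure.** Minimum N = variables × events per variable / event share = 15 × 5 / 0.5 = 150. This reproduces the stated 150, but only with a 50% event share, which the article does not state.

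**2. What governs the bias.** Let B be the outcome's own baseline severity, O baseline ODQ and W walking. With O in the model and B left out, the bias in W follows the partial correlation

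r(B,W | O) = [r(B,W) − r(B,O)·r(O,W)] / √{[1 − r(B,O)²]·[1 − r(O,W)²]}.

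Take r(B,O) = 0.5 and r(O,W) = −0.2. The denominator is √(0.75 × 0.96) = 0.849.

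- r(B,W) = 0: (0 + 0.10) / 0.849 = +0.12
- r(B,W) = −0.1: (−0.10 + 0.10) / 0.849 = 0
- r(B,W) = −0.3: (−0.30 + 0.10) / 0.849 = −0.24

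So the sign can go either way, and the bias can vanish.

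**3. Simulation of the NRPS model with no true walking effect.** From the article: N = 250, success = fall of at least 2.5, ODQ in bands (the top two merged here). Assumed: baseline NRPS mean 5.5, SD 2.5; six-month score = 1.4 + 0.25 × baseline + normal error with SD 2.2; both scores rounded and held to 0–10; ODQ mean 42, SD 16; r(O,W) = −0.2. There were 1,000 runs per setting, and the event share came out at 0.52. Entries are the median odds ratio per SD of walking and the share of runs with p < 0.05 for walking, from the model with walking and banded ODQ.

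| r(B,W) | r(B,O) = 0.3 | r(B,O) = 0.5 | r(B,O) = 0.6 |
|---|---|---|---|
| 0 | 1.06; 5.7% | 1.12; 12.2% | 1.14; 17.6% |
| −0.1 | 0.95; 5.8% | 0.98; 4.9% | 1.00; 4.9% |
| −0.2 | 0.84; 24.4% | 0.87; 18.0% | 0.89; 15.1% |
| −0.3 | 0.74; 59.8% | 0.76; 50.2% | 0.78; 42.7% |
| −0.4 | 0.65; 87.3% | 0.68; 81.8% | 0.67; 81.3% |

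Adding own baseline to the same model gave odds ratios of 0.98 to 1.01 and rejection rates of 4.4% to 6.6% throughout. The Monte Carlo standard error at 5% is √(0.05 × 0.95 / 1,000) = 0.7 percentage points.

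Where walking related to own baseline only through ODQ, the ODQ-adjusted model was nearly unbiased: 6.1% (OR 0.97) with r(B,O) = 0.5 and r(O,W) = −0.3, and 5.5% (OR 0.96) with 0.6 and −0.4.

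**4. PCS.** With success = gain of 6.2, n = 200, 2,000 runs, and assumed baseline SD 8, residual SD 9 and follow-up slope 0.25 to 0.5:

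- r(PCS severity, ODQ) 0.6 to 0.8 and walking at −0.2 with both: rejection 5% to 9%, OR 0.92 to 0.97.
- r 0.7, walking–ODQ −0.3 and walking–PCS severity −0.2: rejection 4%, OR 1.01.

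**5. Room for the extra term.** Counting variables: 16 × 5 / 0.5 = 160. Counting parameters, Table 3 has 1 (walking) + 12 (two-level items) + 2 (procedure) + 4 (ODQ bands) = 19; one more gives 20 × 5 / 0.5 = 200. At a 40% event share the two counts need 200 and 250. At 30% they need 267 and 334, but the existing 15 variables or 19 parameters would already need 250 or 317.

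**The case against.** The strongest reply is that the size rests on correlations that the article does not give. If walking is only weakly related to baseline pain, or related through disability, ODQ does most of the work and rejection stays near 5%. The 50% figure needs walking to track baseline pain more closely (−0.3) than disability (−0.2), although pre-operative mobility is itself measured within the ODQ. Table 3 also offers other covariates that the simulation omits. In a similar run, adding one dichotomised mobility term, with assumed correlations of −0.4 with walking, 0.4 with pain and 0.6 with ODQ, cut rejection from 17% to 11%. All of this stands as a limit on the size; none of it puts own baseline into the models.

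A reader might infer three stronger things, which the documents do not support:

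- **That the bias makes walking look harmful or hides a benefit.** This is one plausible pattern, but the first row of the table shows the reverse.
- **That the NRPS error rates apply to the primary analysis.** The ODQ model has its own baseline as a candidate. PCS and ODQ both measure function, so ODQ may be a closer stand-in for PCS than for pain.
- **That baseline ODQ should be replaced, or baseline pain added to the ODQ and PCS models.** Pre-operative function is a named confounder, and the simulation that supports the fix kept ODQ. No calculation supports adding pain to the other models.

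**Conclusion.** The gap is real and can be read from the article alone: a list fixed at 15 variables, applied to four change outcomes, carries the own baseline of only one, and that one only as a screened candidate. One primary function measure (PCS) and both secondary pain outcomes are affected. If baseline ODQ fails screening, those models may hold no overall baseline severity score at all.

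Neither size nor direction can be asserted. For NRPS, under the assumptions listed, false-positive rates ran from about 5% to well over 50% (87% at the strongest correlation tried), with odds ratios per SD from 0.65 to 1.14. For PCS the assumed settings gave 4% to 9%. These figures show what could happen and do not predict this cohort. The point should be fixed because the remedy is nearly free and removes a possible bias; it does not show that the primary result would be wrong.

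**What to change.** 1. In each of the four models, force in the baseline score of that model's dependent variable (ODQ, PCS, back NRPS or leg NRPS) as a continuous covariate exempt from bivariate screening. In the ODQ model the continuous score takes the place of the bands.
2. Keep baseline ODQ as a candidate confounder in the PCS and two pain models.
3. Amend Table 3 and the confounder section accordingly, and change the count under *Recruitment and sample size* from 15 to 16 variables, stating the event share assumed (160 at 50%).

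**Cost.** No new data and one extra parameter in three models. In the ODQ model, one term instead of four bands saves three parameters. The planned 250 covers the change at a 50% event share on either count. At 40% the full parameter count uses all 250 and leaves nothing for losses, so the assumed share should be stated.

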#### Post-operative activity profile

A seven day activity profile summarising the amount of time spent in sedentary and active postures, time spent walking, a step count, and the number of walks will be generated using the data downloaded from the activPAL3 accelerometers.

#### Factors associated with time spent walking immediately following surgery

Additional data will be collected on a daily basis regarding post-operative back, leg and wound pain intensity (NRPS), the need for supervision while walking, and surgical/medical complications. Reported complications will include events where the participant requires medical intervention in addition to routine post-operative care, and events that limit activity (for example, symptomatic hypotension, analgesia-induced nausea). This information will be sourced from the patient, ward staff, and patient notes. In cases where participants are discharged from the inpatient facility prior to completing the monitoring period they will be asked to record this information daily, which will then be returned to the researchers with the accelerometer following the completion of the monitoring period.

At six months, participants will be asked to report on overall satisfaction with the results of the surgery, scored on a five point likert scale. They will also be asked to describe any post-operative complications experienced after the seven day monitoring period. This will include any event directly related to the surgical procedure requiring medical intervention in addition to routine follow-up care.

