## Method

### Aims

This research will investigate the relationship between the time spent walking in the week following lumbar surgery, and recovery of physical function. The primary aim is to establish whether the amount of walking patients do in the week following lumbar spinal surgery predicts improvement in function at six months. The data collected will also be used to generate an activity profile to describe the overall patterns of activity in the first post-operative week, and to identify factors that may influence the amount of activity patients undertake.

The research questions are:Does the amount of time spent walking during the week after lumbar spinal surgery predict improvement in function at six months?What proportion of time do patients spend performing active tasks (standing and walking) compared to sedentary behaviour (sitting and lying) in the week following lumbar spinal surgery?Is the amount of time spent walking in the first post-operative week influenced by restricted pre or post operative physical function, post-operative pain or complications, or the need for supervision while walking?

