#### Factors associated with post-operative walking time

Bivariate analysis will be used to examine the association between the total time spent walking, and pre-operative mobility, function and physical activity, post-operative back, leg and wound pain, post-operative complications and the need for supervision while walking.

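### Week-1 complications are partly defined by limiting walking and then tested against walking time, so that one association in research question 3 is biased towards finding that complications reduce walking

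*Protocol article*

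**What the plan says.** All places are in the protocol article.

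- **Aims, third research question.** It asks whether week-1 walking time is "influenced by restricted pre or post operative physical function, post-operative pain or complications, or the need for supervision while walking". Complications are one of several factors.
- **Outcome measures, Table 1, post-operative days 1–7.** Early complications are listed as "Complications requiring medical intervention and/or limit walking time". The conjunction makes either criterion sufficient.
- **Factors associated with time spent walking immediately following surgery.** The first criterion is "Reported complications will include events where the participant requires medical intervention in addition to routine post-operative care". The second is "events that limit activity (for example, symptomatic hypotension, analgesia-induced nausea". On the origin of the data: "This information will be sourced from the patient, ward staff, and patient notes". Participants discharged before day 7 record the information themselves each day.
- **Data analysis, Factors associated with post-operative walking time.** "Bivariate analysis will be used to examine the association between the total time spent walking" and a list of factors that includes "post-operative back, leg and wound pain, post-operative complications and the need for supervision while walking". Nothing here or elsewhere splits complications by the criterion they met.
- **Six-month complications.** The same section that defines early complications defines later ones by need for medical intervention only, with no activity criterion.

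**The concern.** An explanatory variable should be ascertained without reference to the outcome it is meant to explain. Here one of the two routes to being recorded as having a complication is that walking was limited. Take two patients with the same nausea and no extra treatment. The one judged to have been held back counts as having a complication, and the other does not. Patients classified this way will tend to have lower walking totals, whatever nausea does to walking in general.

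The study would then report complications as a factor in low walking, and a reader could not tell how much of that came from the recording rule. This matters because the Discussion intends the results to show which patients walk too little and what might be done about it. Covariate adjustment, which is not planned for this analysis in any case, would not remove the problem, because it lies in how the variable is defined.

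**Working it through.** **1. Definition against outcome**

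| Item | Early complications (days 1–7) | Six-month complications |
|---|---|---|
| Qualifies by medical intervention | yes | yes |
| Qualifies by limiting walking or activity alone | yes | no |
| Tested against week-1 walking time | yes | yes |

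Only the early variable shares content with walking time. The other factors in the third research question (function, pain, supervision) are not defined by whether an event limited walking. Table 3 does not list early complications among the 15 variables for the primary model.

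**2. Is there a figure in the plan to reproduce?**

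None is attached to this analysis. The article's minimum sample of 150 belongs to the primary model. It reproduces as 5 × 15 = 75 events and 75 / 0.5 = 150, if half the participants have the event (assumed; no share is stated). The point does not depend on it. The projected sample of about 250 is used below.

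**3. Size under no true effect (all rates are assumptions)**

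- Walking time is standard normal, and no event affects it.
- Medical-intervention event: m = 15% of patients, independent of walking.
- Minor symptom: s = 10%, 20% or 40%, independent of walking.
- A symptom is recorded as limiting with probability a in below-median walkers and b in above-median walkers. The gap between a and b stands for the tendency to attribute low walking to a symptom.

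Probability of being recorded with a complication:

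- below median: pL = m + (1 − m)·s·a
- above median: pH = m + (1 − m)·s·b
- overall: p = (pL + pH)/2

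The mean of a standard normal in each half is ∓√(2/π) = ∓0.798, so the spurious difference in SD units is

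d = −0.798 × (pL − pH) / [2p(1 − p)].

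Example with s = 0.4, a = 0.7, b = 0.3:

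- pL = 0.15 + 0.85 × 0.4 × 0.7 = 0.388
- pH = 0.15 + 0.85 × 0.4 × 0.3 = 0.252
- p = 0.32
- d = −0.798 × 0.136 / (2 × 0.32 × 0.68) = −0.25 (simulated: −0.26)
- share of complications that are limitation-only: 0.85 × 0.4 × 0.5 / 0.32 = 0.53

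Simulated results for N = 250 (2,000 runs per setting, two-sided t-test at 0.05). Each cell gives the spurious walking deficit and the rejection rate:

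| Minor symptom | Limitation-only share | a/b = 0.6/0.4 | 0.7/0.3 | 0.9/0.1 |
|---|---|---|---|---|
| 10% | 22% | 0.04 SD, 6% | 0.09 SD, 10% | 0.17 SD, 19% |
| 20% | 36% | 0.07 SD, 9% | 0.15 SD, 16% | 0.31 SD, 53% |
| 40% | 53% | 0.12 SD, 15% | 0.26 SD, 48% | 0.50 SD, 97% |

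At N = 150 the corresponding rates run from 5% to 82%.

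**4. Controls**

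- With a = b = 0.5 (recording unrelated to walking), the rejection rate at N = 250 is 5% to 6%.
- If only medical-intervention events count, it is 4% to 6% in every setting at both sample sizes.

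The excess therefore comes from the second criterion, and removing that criterion removes it.

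**The case against.** A reader might infer that the whole third research question is circular and its answer built in. The documents do not support that, for three reasons.

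- Complications are one factor among several, and the others do not carry this definition.
- Even for complications, events needing medical intervention qualify whatever their effect on walking.
- The outcome is total accelerometer stepping time over seven days, while the limitation is a report about an event from the patient, ward staff or notes. A patient held back on day 1 can still have a high weekly total, and a low walker without a limiting event is not counted.

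The simulation can also be criticised. Whoever records events does not know whether the patient will end above or below the sample median, and the rates and splits have no source in the article. If limitation were always attributed correctly, an event with no effect would never qualify by that route, and the false-positive rates would not apply. This stands as a limit on the size. It does not restore the test: with perfect attribution, events selected because they reduced walking would be compared with all else, and that cannot show whether such events in general influence walking.

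It might also be inferred that discharged participants decide for themselves what counts as a complication. The article says only that they record the information daily. Who classifies events is a detail that a condensed article may leave to the full protocol. The point does not need it, because the published definition and the published test overlap whoever does the classifying.

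**Conclusion.** The concern holds for the complications component of the third research question only. The direction of the bias follows from the definition: towards complications appearing to reduce walking. Its size cannot be determined from the document. It depends on what share of complications qualify solely by limiting activity and on how strongly that judgement tracks the weekly total. Under the assumed inputs for N = 250, the false-positive rate spans about 6%, which is indistinguishable from nominal, to 97%. Neither end should be read as a forecast.

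The primary analysis of walking and six-month outcome is untouched, and so is the analysis of complications reported at six months. This is one unadjusted association within a secondary question. It is still worth correcting, because as planned its result cannot be interpreted and the remedy is simple.

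**What to change.** 1. On the daily record, note for each week-1 event which criterion it met: medical intervention beyond routine care, limitation of activity, or both.
2. In the bivariate test of walking time, define complications as events needing medical intervention beyond routine care. The article already uses this kind of criterion at six months.
3. Report events that qualify only by limiting activity separately and descriptively, outside the association test.
4. Align the wording of Table 1, the section defining early complications and the analysis section accordingly.
5. Optionally, record a short list of minor symptoms as present or absent each day, whether or not they limited activity. Their association with walking could then be examined without the circularity.

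The cost of steps 1 to 4 is one extra item per event, some rewording, and fewer events in the test, so a less precise estimate. Step 5 adds a brief daily checklist, including for participants already at home. The criterion, and the symptoms if step 5 is adopted, should be captured as events occur, because a symptom that did not limit walking may otherwise go unrecorded and could not be recovered later.
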